**2.2 Describe the significance of the research, and how it will add to existing knowledge**

While free health care is provided for children under five years of age in Zambia, research on the health and well-being of the school-aged population in Zambia is limited. The newly designed SBHP currently piloted in 7 schools in Lusaka offer a potentially effective way to improve the health of students in Lusaka and elsewhere in the country; the aim of this project is to assess the effectiveness of these programs.

In our literature review, we could not identify any other program that utilizes a model similar to the SBHP program; for this reason among others, understanding if this innovative program is achieving its intended purpose is particularly important.

While improving population health through schools has long been a focus of the Zambian Ministry of Education, the SBHP model represents a new approach. School is an appropriate setting for a health intervention in Zambia because school-aged children are the population most affected by infectious diseases, and primary school attendance is as high as 94%.1 Additionally, no other known program utilizes a model similar to HK/BF’s SHW program in which teachers may make referrals to health centers. One program conducted by the Zambian Ministry of Education focused on strengthening teachers’ “professional skills” with in-service teacher trainings and follow-up “professional support”.11 While this program did work on developing leadership skills, it did not emphasize teacher empowerment, a point of the SHW program. Other school-based health interventions in Zambia focus mainly on health curriculum, such as the Nutrition Education in Basic Schools (NEBS) project also led by the Zambian Ministry of Education.10 Teachers in these other programs were also not trained to perform first aid or make referrals.

1. **Study Setting**
   1. **Identify the sites or locations where the research will be conducted.**

This study will be conducted in 14 primary schools in Lusaka district, Zambia.

- 1. **Describe the Principal Investigator’s experience conducting research at study site(s) and familiarity with local culture**The PI has extensive experience in Zambia. He has been conducting research there since 2009, and has established a close working relationship with partners at the University of Zambia as well as the Ministries of Education and Healthth.
  2. **Is the research conducted outside the United States?**

**No** **Yes: If yes; describe site-specific regulations or customs affecting the research, local scientific and ethical review structure**

The study will be conducted in Zambia and will need to be approved by a local IRB as well as the Ministry of Education – our application is currently under review.

- 1. **Are there any permissions that have been or will be obtained from cooperating institutions, community leaders, or individuals, including approval of an IRB or research ethics committee?** **No** **Yes: If yes; provide a list of the permissions (also include copies with the application, if available)**The research is under review by ERES Converge IRB in Lusaka, Zambia.

1. **Study Design**
   1. **Describe the study design type**

This study is designed as a prospective case-control study. Students from the seven intervention schools will be matched with students from control schools; all students will be assessed at baseline (prior to intervention rollout), midline (October) and endline (April 2016).

- 1. **Indicate the study’s duration - and the estimated date of study completion**

The study is projected to last one year. The estimated date of study completion will be June 2016. The proposed timeline is as follows:

| SHW training | April – May 2015 |
| --- | --- |
| Enrollment and baseline survey | May 2015 |
| Intervention rollout | Launch May/June 2015 |
| Midline survey | November 2015 |
| Endline survey & Qualitative analysis | April 2016 |
| Data analysis | May 2016 |
| Final report and data dissemination | June 2016 |

- 1. **Indicate the total number of participants (if applicable, distinguish between the number of participants who are expected to be screened and enrolled, and the number of enrolled participants needed)**

We expect to enroll approximately 1,100 students across 14 schools in this study.

- 1. **List inclusion criteria**

Children attending the 14 schools in the study.

- 1. **List exclusion criteria**

Children not attending any of the 14 target schools.

- 1. **Describe study procedures**

*Sampling*
Fourteen community schools will be involved in the study. In each school, three grades will be selected for the study; in treatment schools, two grades will be randomly selected among those directly taught by SHWs; the grades in the control group will be chosen to match the ones in the treatment group. To be able to link health status directly to standardized tests, all students in grade 7 will be invited to participate in the study in the 14 schools. Intervention schools will receive the SHW Program as well as baseline, midline, and endline health screenings. For each of the seven schools, we will identify a control school within Lusaka district. Control schools will be chosen based on the overall school size, number of pupils in each grade, and average test score performance.

*Outcome measures*
The primary outcome of the study will be child health (prevalence of acute and chronic infection at endline) as well as academic performance (school attendance and grade performance).

The quantitative assessments at baseline, midline and endline will be complemented by qualitative work. For the qualitative component, we will employ a non-probabilistic, stratified purposeful sampling methodology. In our study we will capture the opinions of SHWs, school administrators, mothers and children from a sample of community schools with the SHW program. We will use a mixture of qualitative research methods, namely semi-structured individual interviews and focus group discussions (FGDs).

We will sample a total of 10 SHWs across the seven intervention schools. Of the schools selected, we will randomly sample 3 schools for additional investigation. From this pool of 3 schools we will conduct individual interviews with the school administrators (preferably the headmaster), and FGDs with mothers and children. There will be a total of 3 administrator interviews (1 per school) and 7 FGDs with mothers and children (1 per intervention school).

*Internal validity*
In order to ensure that schools or students are not systematically different prior to the launch of the study (which could occur given the small sample sizes), classes and schools will be matched based on the overall school and class size, as well as the most recent school test performance. For each treated class, the most comparable class from the control group will be selected. A total of approximately 80 children (25-30 from each grade) will be enrolled from each school – all students in selected grades will be invited to join the study; final sample size will depend on class sizes as well as parental consent.

*Study interventions*
The study will assess (but not be directly involved with the delivery of) a combined intervention package currently implemented by a local NGO called Angels of Mercy. The program has two components:
1. The School Health Worker (SHW) Program. The aim of the SHW training is to empower teachers to recognize and refer children in need of medical attention, give basic first-aid care, and run health education lessons. Over the past year, HK/BF has worked with government officials and medical professionals in Zambia to develop a 10-day, 100-hour SHW training adapted from the Community Health Worker model. The curriculum trains teachers as front-line health workers capable of running health education lessons, recognizing and referring children in need of care, and providing first-line care.

Training sessions are facilitated by a group of health educators from the Ng’ombe Health Centre, all of whom have been certified by the Ministry of Health. The team of health educators consists of an environmental health-technician, clinician, clinic in-charge, and nutritionist. Additionally, all teachers are required to undergo twenty hours of clinical sessions at the Ng’ombe health centre, wherein they examine sick youth under the supervision of a clinical officer. Teachers receive K40 daily travel allowance (~$6) during training. The facilitation team from the Ng’ombe clinic meets with all of the SHWs at least once a month at their regular monthly meeting. During the meeting, the team is able to collect all forms from the teachers, assist the teachers to overcome challenges they have encountered, and add supplementary training lessons. The teachers are provided with a K100 monthly allowance (~$17), as well as shirts, bags, and SHW cards (which give them preferential care at the clinic).
Pre/post tests are conducted for all of the teachers in the SHW program. This test is re-administered at the ninety-day and half-year mark in order to measure how much information was retained by the teachers. Additionally, HK/BF and the Ng’ombe Health Centre collect a number of forms form the teachers and the health clinic in order to assess the performance of the teachers in their SHW roles. These include referral and feedback forms, examination registries, and health education reviews.
Selection of teachers for the training is done by the participant schools and the Ng’ombe Health Centre. The schools are able to nominate a pre-determined number of teachers to be interviewed by the in-charge and training facilitators from the Ng’ombe clinic. Following the interview, the clinic staff consults the school admin to select teachers to attend the training. The number of teachers trained from each school is dependent upon the number of pupils enrolled at the school. Schools with less than 200 pupils are able to send one teacher for training, schools with greater than 200 pupils send 2 teachers for training and schools with greater than 400 students are able to send 3 teachers. The target ratio for the program is at least 1 teacher for every 200 students.
School administrators will be trained for 45 hours on how to supervise, manage, and motivate school health workers, design school-wide health education curricula, and improve school WASH conditions. All school administrators receive a daily K50 travel allowance (~$8) for attending training and graduating administrators receive a t-shirt and certification.
2. Bi-annual school based preventive health screening days. In collaboration with the Ministry of Health bi-annual health screening days will be conducted at all target community schools. All health screenings will be conducted by nurses and clinical officers from the local government health clinic and supported by trained SHWs. Parents or guardians are expected to attend screening days with their children and informed consent is required by both the child and guardian. As part of the screening, a complete physical examination is performed including urine screening for schistosomiasis, which is endemic in the region. All children receive a dose of vitamin A, mebendazole for presumptive deworming, and, if indicated, Praziquantil for schistosomiasis. Medication for simple acute ailments will be dispensed to the guardian of sick pupils upon the completion of the health screening. All students with chronic or severe ailments will be referred to the local health centre. AoM offers health screenings to all students within a class and are not limited to the students whom will participate in the study.
*Control group:* 7 schools will be used as the control group. All control schools will complete a baseline survey including height/weight, mid upper-arm circumference, and self-reported health at baseline, as well as an endline survey including a complete health screening.

- 1. **Does the study involve the collection of data/specimens (including the use of existing data/specimens)?**

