**No** **Yes: If yes; describe the circumstances as well any associated procedures to ensure orderly termination**

1. **Data/Statistical Analyses Plan**
   1. **Briefly describe the plan for data analysis (including the statistical method if applicable)**

All outcome variables will be compared between treatment and control groups, controlling for baseline covariates observed. To control for within-school correlations, all standard errors will be clustered at the school level.Qualitative data will be analyzed using Grounded Theory, beginning with open coding, and following an iterative coding process.13 First, we will subject all data (SHW interviews, school administrator interviews, and both mother and student FGDs) to an open-coded process without prior assumption of theoretical frameworks. From this, key themes will be deduced and a codebook of these themes will be created. Codes will be generated and assessed using the qualitative analysis program NVivo.

- 1. **Is there a sample size/power calculation?**

**No** **Yes: If yes; describe the calculation and the scientific rationale, and, if applicable, by site and key characteristics such as participant demographics**

We expect a total sample size of approximately 1120 students across the 14 schools. The primary outcome will be pupil health, measured by the presence of any acute or chronic infection. The study is powered to detect a decline in infection prevalence from an expected baseline level of 0.50 to 0.35, assuming a design effect of 2 as well as an attrition rate of 10% over the study period. The secondary outcome of the study is academic performance; the primary measure we will use is days of school missed; the study is powered to detect a 20% increase in the proportion of students not missing any schooling.

1. **Recruitment Methods**
   1. **Does the study involve the recruitment of participants?**

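### The protocol contradicts itself on whether the seven intervention schools are unexposed at baseline; if they are not, matching and adjustment would remove part of any academic effect already achieved.

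*Protocol*

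**What the plan says.** On timing, Study Design (study design type) states that "all students will be assessed at baseline (prior to intervention rollout), midline (October) and endline (April 2016". The timeline in the same section has the rows "SHW training | April – May 2015" and "Enrollment and baseline survey | May 2015", followed by a launch in May or June 2015.

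On the state of the programme, in a protocol dated 21 April 2015:

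- Specific Aims names teacher training as one of the programme's two components and describes the programme as being piloted now.
- Section 2.1, on the new School Health Worker (SHW) programme, reports that it has already been piloted in the Ng'ombe area.
- Section 2.2 speaks of "The newly designed SBHP currently piloted in 7 schools in Lusaka" and, in the same sentence, gives the project's aim as assessing these programmes.
- Study Design, Study interventions, calls what is assessed "a combined intervention package currently implemented by a local NGO called Angels of Mercy".

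On protection from bias, Study Design, Internal validity, says that "classes and schools will be matched based on the overall school and class size, as well as the most recent school test performance". The Data/Statistical Analyses Plan compares the arms while "controlling for baseline covariates observed".

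**The concern.** Schools are not randomised. The case that the arms are comparable therefore rests on two devices: choosing similar control schools and classes, and adjusting for baseline values. Both assume that the values used were not yet touched by the programme.

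The protocol asserts this for the baseline survey but describes the programme in terms that put it in doubt. For the test results used in matching, it sets no date other than that they be the latest available. If the intervention schools were already exposed, these values carry some programme effect in one arm and none in the other. Conditioning on them would subtract that effect from the academic comparison (aim 3). Once control schools have been chosen on such scores, the analysis cannot easily undo it.

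**Working it through.** The protocol gives no figure on this point to reproduce. The check compares the passages and then follows the consequence algebraically.

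**Step 1: can the passages be read together?** Three readings are open.

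- *Reading A.* The seven pilot schools are the seven intervention schools, and the programme was active there before baseline. In favour: the number is the same; section 2.2 identifies the piloted programmes as those to be assessed; the intervention schools are treated as already fixed while controls are still to be identified; and monthly SHW meetings and allowances are described in the present tense.
- *Reading B.* The pilot ran in other schools, and the intervention schools were first reached by the training in April 2015.
- *Reading C.* The current pilot is the one whose training began in April 2015, so pupils had no earlier exposure.

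In favour of B or C: the explicit statement that baseline comes first, and the future tense used for delivering the SHW programme to intervention schools, training administrators and holding screening days. The text does not decide between the three.

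**Step 2: what the timeline shows under every reading.** Training (April to May) starts before the baseline month and may run through it, and launch may fall in that same month. By the definition in Specific Aims, one component has therefore begun by the time of baseline. This is weaker evidence than the pilot wording, because training teachers does not by itself treat or teach pupils.

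**Step 3: consequence under reading A.** Let

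- Δ = programme effect already present in the intervention school's earlier score;
- ρ = persistence, the change in expected endline outcome per unit of earlier score within an arm;
- τ = total programme effect at endline.

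A control matched closely on the observed score has an untreated level higher by Δ than that of its intervention school. At endline this advantage is worth ρΔ, so

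expected contrast = τ − ρΔ.

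Regression adjustment gives the same expression, with ρ the coefficient of the baseline covariate. At ρ = 0 nothing is lost; at ρ = 1 all of Δ is lost. Matching here is to the most comparable class on several variables, so it is not exact and the loss through matching may be smaller. Under readings B and C, Δ = 0 and the loss is zero. The documents give neither Δ nor ρ, so no numerical size follows.

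**Step 4: which variables are concerned.** Of the matching variables, only test performance could plausibly have been changed; school and class size are unlikely to have been. Among the adjustment covariates, the concern is baseline attendance and marks. Examined infection cannot be a baseline covariate in both arms, because control schools have only anthropometry and self-reported health at baseline (Study Design, Control group).

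**The case against.** The strongest reply is that the protocol says outright that baseline precedes rollout, and no passage says that the pilot schools are the intervention schools or that any pupil was reached before May 2015. In a document dated 21 April 2015, calling the programme a current pilot may mean no more than training that began that month. This stands: prior exposure is an inference, and the point can only be conditional.

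Four stronger readings may tempt a reader, and the documents do not support them.

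- *That baseline definitely follows programme start for pupils.* See above.
- *That the endline contrast is misreported as a one-year effect.* The protocol says that the study lasts about a year and promises no one-year effect. On its own dates, launch to endline is between 276 days (30 June 2015 to 1 April 2016; 276 / 30.44 = 9.1 months) and 365 days (1 May 2015 to 30 April 2016; 365 / 30.44 = 12.0 months).
- *That baseline attendance is distorted because teachers were away at training.* The protocol gives no recall window for attendance and does not say whether training fell in school time or whether classes went uncovered.
- *That the infection outcome is biased.* Earlier exposure would lengthen the exposure behind the endline contrast, which would still compare programme with no programme. That is a matter of labelling.

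It may also be said that the remedy is premature until exposure is shown. But controls are chosen once, and anchoring the scores costs little if there was no earlier exposure.

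**Conclusion.** The contradiction is in the text and should be resolved, preferably before control schools are selected. It does not establish that the study is biased.

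If the intervention schools had programme contact before baseline, matching and adjustment would take ρΔ off the total academic effect, somewhere between none and all of the effect already achieved when 0 ≤ ρ ≤ 1. For a beneficial programme this pulls the academic estimate towards no effect. If they had no earlier contact, the loss is zero and only wording needs correcting. The conclusion rests on two assumptions: that any earlier contact was long enough to change scores or attendance, and that the target is the programme's whole effect rather than the increment since May 2015. The documents establish neither the first assumption nor a numerical size.

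**What to change.** 1. State the date of first programme contact for each intervention school. Reconcile the statements in section 2.1 (earlier pilot), section 2.2 (seven pilot schools), Study Design (baseline before rollout, and the timeline) and Study interventions (package already running).
2. Under Internal validity, replace the undated test criterion with test performance in the last term completed before that school's first programme contact, and use the same term for its matched control. Take baseline attendance and marks from same-term school records in both arms where available, and use these for adjustment.
3. If any intervention school was exposed before May 2015, remove the statement that baseline precedes rollout, describe the endline contrast as the running programme versus none, and report prior exposure by school.

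The cost is protocol wording and extraction of one earlier term of existing records in 14 schools. The downside is small: some earlier records may be incomplete or may not cover newly enrolled pupils. The protocol itself describes pupil self-report verified by school staff, so usable pupil-level records should be confirmed first.

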**No** **Yes: If yes; indicate how, when, where and from whom specimens or data will be obtained**

*Data collection instruments*
The study will use standard questionnaires for data collection. In addition to a full set of anthropometric measures (height, weight and mid-upper arm circumference) participants will be asked about their recent health history, health service access and treatment seeking. Students will also be asked to report on their own school performance. Teachers and school administrators will be asked to verify the scholastic performance of all students within the study.

*Midline and Endline assessment*Two rounds of follow-up assessments will be done: one in November 2015, and one in April 2016.

*Qualitative interviews and focus group discussions*
We intend to conduct semi-structured interviews with 10 SHWs in order to ask specific questions about the components of empowerment as established by the frameworks provided by the World Bank and CARE on measuring empowerment based on agency, structure and relations.12,13 We will sample one school administrator per school and conduct semi-structured interviews to elicit information about his or her perceptions of the SHWs' empowerment. These interviews can then be compared with those from the SHWs on their own sense of empowerment so we can better understand the difference between perceived and self-identified empowerment. To ensure that our interviews capture the concept of empowerment as it applies to this population, we will review the transcripts from the interviews as they are completed and make any necessary changes to protocol as the need arises.

Separately, we intend to conduct FGDs with mothers and children in order to investigate their perceptions of SHW empowerment. A focus group size of 8 will maximize the balance between too small, possibly limiting the chances of a lively and informative conversation, and too large, where that some voices might be drowned out and the conversation could veer off track.

- 1. **Is there a data and safety monitoring plan (required for greater than minimal risk studies)?**

